| Aims                                | 
Aim 1 examines the efficacy as assessed by the Columbia Suicide Severity Rating Scale (C-SSRS) severity of ideation subscale of sequential bilateral aTBS compared to sham stimulation over 10 days of active treatment and 12 months of follow-up. Aim 1 will also examine the impact of active vs sham sequential bilateral aTBS treatment on the number of emergency department visits and hospitalizations related to suicidality.
 
Aim 2 examines a biomarker of cortical inhibition called long interval cortical inhibition (LICI). It is expected that LICI will have an indirect relationship with severity of suicidal ideation as assessed with the C-SSRS severity of ideation subscale in all subjects at baseline. It is also expected that in adolescent subjects receiving active sequential bilateral aTBS treatment there will be an indirect relationship between LICI and the C-SSRS severity of ideation subscale over 10 days of treatment.
 
Exploratory aims focus on the development of TMS-EEG measures of cortical inhibition.
 |
| Number of Subjects                  | 80                                                                                                                                                                                                                                                                                                                                                                                                                                                                                                                                                                                                                                                                                                                                                                                                                                                                                                                                                                                                                                                                          |

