In preparation for study design our group reviewed current literature examining accelerated TMS protocols and published a meta-analysis (Figure 5). There was variability in published protocols. Summary analysis of three randomized controlled trials yielded an effect size (Hedges' *g*) of 0.4. Another analysis of all active arms and open-label studies revealed an effect size (Hedges' *g*) of 1.3. Preliminary results suggested that aTBS improved suicidal ideation in adults with MDD.

[figure not shown]

Figure 5. Prior studies of accelerated TMS

[figure not shown]

Figure 6. Indexing suicidal ideation with long-interval cortical Inhibition (LICI) biomarkers

that depressed adolescents with suicidal behaviour have impaired LICI and GABAB mediated inhibition compared to depressed adolescents with no history of suicidal behaviors and healthy controls. Please note that larger LICI values denote diminished inhibition (Figure 6). In another longitudinal study of suicidal adolescents in treatment for depression, enhancements in LICI measures correlated with improvements in suicidal ideation (assessed with the C-SSRS subscale for severity of suicidal ideation) after controlling for depression severity. Other recent work demonstrated the utility of TMS-EEG measures of LICI and N100 as target engagement biomarkers for brain stimulation interventions of suicidal ideation in adults with

The paired-pulse paradigm LICI provides an index of GABAB receptor mediated inhibition. A suprathreshold test stimulus is applied to the motor cortex eliciting a motor evoked potential (MEP) in the contralateral abductor pollicis brevis electrode. During LICI testing, suprathreshold conditioning and test stimuli are applied with interstimulus intervals (ISIs) of 100-200 ms which results in a MEP of diminished amplitude. This resultant inhibition is mediated by GABAB receptors. Our prior studies demonstrate

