| YMRS-Young Mania Rating Scale                                                        | This is an 11-item measure used to assess for manic symptoms. The YMRS scale will be completed at baseline and repeated during the course of study participation if symptoms of mania occur in a study subject. If the YMRS is positive, A MINI/MINI-Kid will be repeated to evaluate for mania. If the study subject meets full DSM-5 criteria for mania or hypomania he or she will be discontinued from the study and followed clinically.                                                                                                                                                                                                                                                                                                                                                                                                                                                                                                                                                                                                |
| TMS Neurophysiology Measures                                                         | TMS-EMG (LICI-100) and TMS-EEG (LICI-100 and N100) neurophysiology measures will be collected in adolescent subjects at baseline and after the final day of sequential bilateral aTBS.
25, 81                                                                                                                                                                                                                                                                                                                                                                                                                                                                                                                                                                                                                                                                                                                                                                                                                                                           |

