**Neurophysiological TMS:** Neurophysiological TMS procedures (LICI-100 is the primary outcome measure) will be conducted at Mayo Clinic with our standard protocols that have been published previously. Relaxation will be monitored with audio feedback. Surface EMG readings are collected from the abductor pollicis brevis (APB) muscle. The TMS-EMG panel includes LICI, SICI, intracortical facilitation (ICF), and the cortical silent period (CSP) counterbalanced to avoid order effects. Note that SICI, ICF, and CSP are collected for exploratory analyses and are not the focus of the present grant specific aims. The primary outcome measure is LICI-100 (LICI with an ISI of 100 ms). The TMS-EEG recordings (for LICI-100 and N100 as examined in prior studies of adults) will be acquired through a 64-Channel EEG (EGI Foundation) System in accordance with prior published protocols (that have yielded high test-retest reliability with an intraclass correlation coefficient greater than 0.9). In light of recent controversies and publications, the protocol will include a realistic sham (scalp and auditory stimulation) to account for peripheral multisensory stimulation. A foam sponge will be placed between the coil and the EEG cap to reduce tactile artifact. Foam earphones and white noise cancellation will be used to mask the auditory click that occurs with TMS, thereby mitigating auditory artifact.

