### Primary Aim

#### Data Analysis Plan for Primary Aim 1 (Hypotheses 1a–1c)

##### Primary Outcome for Aim 1: Suicidal Ideation during the 10-day acute Trial Period

**Hypothesis 1a:** We expect 10 days of sequential bilateral aTBS will have greater efficacy for improving suicidal ideation in adolescents with MDD (as assessed by the C-SSRS severity of ideation subscale) over the 10-day acute treatment trial compared to sham stimulation.

Suicidal Ideation (as measured by the C-SSRS severity of ideation subscale) over the 10-day acute sequential bilateral aTBS trial period will be the primary ordinal outcome measure. The acute change over time (10 days) in Suicidal Ideation will be compared between the two treatment groups (sequential bilateral aTBS vs. sham stimulation) using an ordinal logistic regression model within a Generalized Estimating Equation (GEE) framework. The logistic model will contain fixed effects terms for treatment, time, treatment  $\times$  time interaction along with baseline C-SSRS severity of ideation subscale as a covariate. Age, sex, pubertal status, antidepressant medication status, and depression severity (CDRS-R total as a time-varying covariate) will also be included as covariates in the model. Simple treatment group effects in each time period will also be assessed. [see sensitivity analysis section below for missing not at random (MNAR) mechanism].

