#### Secondary Ordinal Outcome for Aim 2: Suicidal Ideation during the 10-day acute Trial Period

**Hypothesis 2b:** We expect that, among the adolescents who receive active sequential bilateral aTBS treatment, there will be an indirect relationship between cortical inhibition (as assessed by LIC1-100 collected with TMS-EMG) and suicidal ideation (as assessed by the C-SSRS severity of ideation subscale) over the 10 day acute treatment trial.

An ordinal logistic regression model within a GEE analysis framework similar to that described above for Hypothesis 1a will be used here to examine the relationship between cortical inhibition (LIC1-100 collected with TMS-EMG as a time-varying covariate) and C-SSRS severity of ideation subscale (as the response variable) over the 10-day acute treatment trial. The parameter estimates (regression coefficients) will be interpreted from the solution for fixed effects in the GEE analysis. The adjusted odds ratio (i.e., odds of suicidal ideation from cortical

inhibition), and 95% confidence interval, will be estimated as part of the GEE model. The same covariates specified above in Hypothesis 1a will be included in the model for Hypothesis 2b.

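### The single time-varying LICI coefficient in Hypothesis 2b mixes differences between subjects with change within subjects, so a positive result would not by itself show target engagement

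*Protocol*

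**What the plan says.** The Study Summary states the hypothesis: in the active arm, "there will be an indirect relationship between LICI and the C-SSRS severity of ideation subscale over 10 days of treatment". Section 7.2 gives the model, an ordinal logistic GEE like that of Hypothesis 1a, with "LIC1-100 collected with TMS-EMG as a time-varying covariate". It also says what counts as the result: "The parameter estimates (regression coefficients) will be interpreted from the solution for fixed effects in the GEE analysis", together with an adjusted odds ratio and 95% interval.

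On adjustment: "The same covariates specified above in Hypothesis 1a will be included in the model for Hypothesis 2b". Through 1a these are time, "along with baseline C-SSRS severity of ideation subscale as a covariate", time-varying CDRS-R total, age, sex, pubertal status and antidepressant status. Baseline LICI is not listed, and LICI is not split into a level and a change.

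Table 4 (section 6.4) says the "neurophysiology measures will be collected in adolescent subjects at baseline and after the final day of sequential bilateral aTBS". That is two LICI values per subject, while the C-SSRS is rated daily. Hypothesis 3b uses the same model for the TMS-EEG markers.

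Section 2.2 gives Aim 2 two purposes, prediction and target engagement. Section 1.4 separates the baseline correlation with ideation from later target engagement.

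**The concern.** Hypothesis 2a covers the cross-sectional association at baseline, in all subjects. What 2b adds, given its restriction to treated subjects and the target-engagement purpose, is whether a subject's ideation moves with that subject's own LICI. The longitudinal evidence in section 1.4 is of this kind: "enhancements in LICI measures correlated with improvements in suicidal ideation".

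One marginal coefficient for a time-varying covariate does not isolate that. Suppose adolescents with weaker inhibition simply tend to have more ideation throughout. The coefficient then departs from zero even if nobody's ideation follows their own change in LICI. The risk is greatest when 2a is true, because 2b could then look like separate confirmation of target engagement. Section 2.1 presents the trial as a basis for pivotal studies, so that reading could be carried forward.

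**Working it through.** **Plan's own figures.** The protocol gives no sample size or power for 2b. The 1a figure of 35 per group reproduces. An odds ratio of 2.85 on a sham proportion of 0.50 gives 2.85/3.85 = 0.740. Two-sided 0.05 and 80% power need 63 per arm. The repeated-measures factor is (1 + 9 × 0.5)/10 = 0.55, and 63 × 0.55 = 34.65, so 35. This point does not affect that calculation. The figure of 35 is used below as the evaluable active arm.

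**Share of LICI variance between subjects.** Scale the LICI variance to 1. With two values per subject, the variance around the subject's own mean is (1 − ICC)/2. The between-subject part is ICC + (1 − ICC)/2 = (1 + ICC)/2.

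| LICI ICC (assumed) | Between-subject share |
|---|---|
| 0.3 | 65% |
| 0.5 | 75% |
| 0.7 | 85% |
| 0.9 | 95% |

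The protocol does not say how two LICI values map onto ten daily ratings. If the baseline value is carried over days 1 to 9, the within-subject part is 2 × 0.9 × 0.1 × (1 − ICC) = 0.18(1 − ICC). At ICC 0.5 the between-subject share is then 91%. Under an exchangeable working correlation of about 0.25, the between-subject weight falls, to 54% or more with two rows per subject and about 62% to 94% with carry-forward.

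**Effect of adjusting for baseline C-SSRS.** In a linear model with ICC 0.7 and level correlation 0.5, the single coefficient averages 0.39 without the adjustment and 0.23 with it, a reduction of 1 − 0.23/0.39 = 41%. Over the settings tried, the reduction was roughly 30% to 45%.

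**Simulation with no within-subject link.** Inputs: 35 active subjects, ten daily ordinal ratings, ideation correlation 0.50 (the value in section 7.1), and LICI at baseline and post-treatment only. Stable levels of LICI and ideation correlate. LICI change is independent of ideation. The model is an ordinal GEE with independence working correlation, robust variance and t reference, including time, baseline C-SSRS, time-varying CDRS-R and three further covariates. There were 1000 runs per setting, rejecting at two-sided 0.05.

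| LICI ICC | Level correlation | Single coefficient rejects | Within-subject term after split rejects |
|---|---|---|---|
| 0.7 | 0 | 8% | 8% |
| 0.5 | 0.3 | 18% | 10% |
| 0.5 | 0.5 | 36% | 10% |
| 0.7 | 0.3 | 22% | 9% |
| 0.7 | 0.5 | 48% | 9% |
| 0.9 | 0.5 | 59% | 9% |

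The first row shows the small-sample floor of about 8%. After LICI is split into subject mean and deviation, the within-subject coefficient centres on zero (−0.02 to 0.00) and stays near that floor.

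**Other models.** A linear GEE with exchangeable correlation, without CDRS-R, gave 9% to 48% for the single coefficient where level correlation was 0.3 or 0.5, and 4% to 6% for the within-subject term. A linear model of the post-treatment rating alone, adjusted for baseline score, gave about 8% to 32% against 5% for level correlations of 0.3 to 0.6. In that model, using baseline LICI plus change left up to about 9% rejection for the change term. Using mean LICI plus change held it at 5%.

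**The case against.** **LICI may not be stable.** A reader might infer that LICI is a fixed trait, from "high test-retest reliability with an intraclass correlation coefficient greater than 0.9" in section 6.4. That figure describes TMS-EEG recordings in earlier protocols, not TMS-EMG LICI-100 under aTBS. Sections 1.1 and 1.4 treat LICI as changing with treatment. This objection stands, and the point does not need the trait claim: the share exceeds 50% at any positive ICC.

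**2b is not 2a again.** A reader might infer that 2b repeats 2a. It does not. Hypothesis 2a uses all subjects before treatment. Hypothesis 2b uses the active arm, on-treatment ideation and adjustment for baseline ideation. A between-subject result in 2b would say that LICI relates to later ideation beyond its baseline level, which is useful for prediction. It still would not be target engagement.

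**Measurement frequency matters.** It would be wrong to say the blend is equally serious however often LICI is measured. With k values the share is ICC + (1 − ICC)/k. At ICC 0.5 it falls from 75% at k = 2 to 55% at k = 10. This trial has two.

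**The wording says relationship, not change.** True, and section 1.4 cites cross-sectional evidence too. Only the target-engagement purpose and the restriction to treated subjects call for the within-subject reading.

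**This could be left to the analysis plan.** The way LICI is aligned to days could be. The protocol, however, already fixes one time-varying term and says its coefficient is the result.

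**Conclusion.** The concern holds in this form: the 2b coefficient blends two associations, and a significant value cannot by itself be read as LICI tracking response to aTBS. That follows from the model and needs no assumed figure.

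The size does need assumptions. For LICI ICC of 0.5 to 0.9 and level correlation of 0.3 to 0.5, neither given in the protocol, false support for a within-subject link arises in about 18% to 59% of trials in the planned type of model, against a floor of about 8%. The range is lower, about 8% to 32% against 5%, if only the post-treatment rating is analysed. With no correlation between stable levels there is no inflation above the floor.

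This concerns a secondary biomarker hypothesis, and 3b, which copies it. The primary comparison and its sample size are untouched. It should be changed before analysis.

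**What to change.** In section 7.2, for 2b and likewise for each TMS-EEG marker in 3b:

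- Replace the single biomarker term with two: the subject's mean LICI-100 (average of baseline and post-treatment) and the change from baseline to post-treatment.
- Use the post-treatment C-SSRS severity rating as the outcome, adjusted for baseline C-SSRS and the other planned covariates, because LICI is not observed on days 1 to 9.
- State that the target-engagement reading is judged on the change term, and that the mean term is reported as a between-subject association only.

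Mean plus change is preferable to baseline plus change, which leaves some of the level association in the change term.

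**Cost.** One extra covariate and a few sentences. The daily ratings between the two LICI measurements drop out of this test. The interval for the change term is wider when LICI is reliable. The SD of change is √(2(1 − ICC)) times the SD of LICI: 1.00, 0.77 and 0.45 for ICC 0.5, 0.7 and 0.9. Other things equal, the standard error per unit of LICI is 1/1.00 = 1.0, 1/0.77 = 1.3 and 1/0.45 = 2.2 times that for a level term. With about 35 subjects the change term may be imprecise, and the protocol should say so.

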| 
Statistical
Methodology
 | 
Suicidal Ideation as measured by the Columbia-Suicide Severity Rating Scale (C-SSRS) severity of ideation subscale over the 10-day sequential bilateral aTBS trial period will be the primary ordinal outcome measure. The acute change over time (10 days) in Suicidal Ideation will be compared between the two treatment groups (sequential bilateral aTBS vs. sham stimulation) using an ordinal logistic regression model within a Generalized Estimating Equation (GEE) framework. The logistic model will contain fixed effects terms for treatment, time, treatment <math>\times</math> time interaction along with baseline C-SSRS severity of ideation subscale as a covariate. Age, sex, pubertal status, antidepressant medication status, and depression severity (CDRS-R total as a time-varying covariate) will also be included as covariates in the model. Simple treatment group effects in each time period will also be assessed. In particular, we will examine for “rapid-acting” treatment effects on day 2 and day 3 of the 10-day aTBS protocol. Maximum likelihood estimation and Type 3 tests of fixed effects will be used along with the best fitting covariance structure. The sandwich (robust covariance matrix) estimator will also be considered. For the ordinal logistic regression, the cumulative probabilities will be modeled over the lower-ordered suicidal ideation scale scores (less suicidal ideation). The adjusted odds ratio (i.e., odds of suicidal ideation from treatment status), and 95% confidence interval, will be estimated as part of the GEE model so as to interpret the omnibus treatment effect. The odds ratio will also be interpreted as the effect size estimator for the between-subjects treatment effect. The PROC GENMOD procedures (along with maximum likelihood estimation) in SAS software will make use of all available data from all participants from the efficacy analysis set, and provide a robust mechanism for handling data that are assumed missing at random.
 |

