## 7 Statistical Plan

### 7.1 Sample Size Determination

#### Sample Size Estimation and Power Analysis for the Primary Aim of the Study

We established the sample size for the Primary Aim/Outcome/Hypothesis 1a (suicidal ideation over 10 days of acute sequential bilateral aTBS treatment) by incorporating a repeated measures design, with assumptions about potential participants (e.g., effect size/odds ratio), based on general guidance from a recent study that evaluated the effect of bilateral rTMS vs. sham stimulation on suicidal ideation in adult patients with treatment-resistant MDD. The results of the *a priori* sample size estimation and power analysis suggest that a sample size of 35 participants per group (N=70) achieves 80% power, at a 0.05 alpha level (two-tailed), to detect an overall odds ratio of 2.85 (sequential bilateral aTBS vs. Sham stimulation on lower-ordered intensity of suicidal ideation CSSR-S subscale scores—less suicidal ideation) in a 2 (between-subjects) group randomized design with 10 (within-subjects) repeated measurements of the primary ordinal outcome (suicidal ideation), when the proportion (or incident rate) of suicidal ideation from the sham group at the end of the 10-

day trial  $\geq 0.50$ , and the assumed within-subject correlation between observations (suicide ideation) on the same subject is  $\leq 0.50$  (0.50 was based on guidance from our preliminary TMS work). We note that the posited odds ratio of 2.85 for the current application is a bit more conservative than what was reported in the Weissman, et al. (2018) study of bilateral TMS vs. Sham stimulation on suicidal ideation in adult patients with treatment-resistant MDD (odds ratio=3.03).

We anticipate some dropouts (~10% based on treatment discontinuation results from our previous rTMS studies). Thus, ~80 participants will be enrolled to allow for this expected rate of attrition with the intent of capturing a range of evaluable data for 70 participants. The Power Analysis and Sample Size (PASS) 2019 software, version 14.0.15, was used to carry out the sample size and power analysis (PASS 2016, NCSS, Inc., Kaysville, Utah).

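### If the GEE sandwich variance is used without a small-sample correction, the interval for the active-arm LICI odds ratio (H2b), and mildly that for the overall treatment odds ratio (H1a), is too narrow

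*Protocol*

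**What the plan says.** The Study Summary (Statistical Methodology) and Section 7.2 specify an ordinal logistic GEE for Hypothesis 1a. Its terms are treatment, time, their interaction, baseline C-SSRS ideation severity, and further covariates: "Age, sex, pubertal status, antidepressant medication status, and depression severity". The Study Summary names PROC GENMOD and Type 3 tests, and reports an adjusted odds ratio with a 95% confidence interval as the effect size. On the variance it says "The sandwich (robust covariance matrix) estimator will also be considered". The Hypothesis 1a text in Section 7.2 names no variance estimator. Neither place names or rules out a small-sample correction, says whether the Type 3 tests are Wald or score tests, or says whether time is categorical or linear.

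Hypothesis 2b uses a similar model with the same covariates, but only "among the adolescents who receive active sequential bilateral aTBS treatment", with LICI-100 as a time-varying covariate. Tables 3 and 4 show LICI measured twice, at baseline and after the last treatment day.

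On numbers, Section 7.1 states that "a sample size of 35 participants per group (N=70) achieves 80% power", with about 80 enrolled. Section 7.3 defines one population, all treated subjects, so up to 80 (40 active under 1:1 allocation) could enter the models.

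**The concern.** The sandwich estimator is justified in large samples of independent clusters, and here the cluster is the subject. With few subjects and a model that fits them closely, the residuals are too small and the estimated variance is biased downward. A Wald test or interval built on it then rejects too often and covers too little. At 70 to 80 subjects some effect is plausible. At 35 to 40, with the full covariate list carried over, it should be larger.

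The affected quantities are the efficacy odds ratio and the biomarker odds ratio. Any error runs toward false positives and weighs most on the target-engagement claim. Section 2.1 says this pilot is meant to support pivotal studies, so a spurious biomarker signal would be carried forward.

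**Working it through.** **The plan's own figure.** Section 7.1 assumes two-sided alpha 0.05, 80% power, an odds ratio of 2.85, sham proportion 0.50, 10 repeated measurements and within-subject correlation 0.50.
- Active proportion: 2.85 / (1 + 2.85) = 0.740.
- Repeated-measures factor: (1 + 9 × 0.50) / 10 = 0.55.
- Two-proportion formula with pooled variance, times 0.55: 34.6, so 35 per group.
- Dropout: 70 / 0.90 = 77.8, so 78, consistent with about 80 enrolled.

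The sample size reproduces and is not affected by this point.

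**Parameter counts.** Five cut-points are assumed (four if a score of 0 is not used) and one parameter per covariate.
- H1a, categorical time: 5 + 1 treatment + 9 days + 9 interactions + 6 covariates = 30. Linear time: 5 + 1 + 1 + 1 + 6 = 14.
- H2b, categorical time over 10 days: 5 + 9 + 1 LICI + 6 = 21. Linear time, or only the two occasions when LICI is measured: 5 + 1 + 1 + 6 = 13.

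**Null simulation.** Cumulative-logit GEE, independence working correlation, six outcome levels, realised within-subject correlation about 0.52, the protocol's covariates, 2,000 to 2,500 runs per setting. These data-generating choices are assumptions. Monte Carlo standard error is about 0.5 to 0.7 points. MD is the Mancl-DeRouen correction with a normal or chi-square reference. Rejection rates at nominal 5%:

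| Test | Subjects / parameters | Uncorrected sandwich, Wald | Generalized score | MD |
|---|---|---|---|---|
| H1a overall effect | 70 / 30 | 8.2% | 6.9% | 4.9% |
| H1a overall effect | 70 / 14 | 8.2% | 6.9% | 4.7% |
| H1a overall effect | 80 / 30 | 6.9% | 5.9% | 4.4% |
| H1a interaction, 9 df | 70 / 30 | 11.4% | 3.7% | 8.8% |
| H1a day 2; day 3 | 70 / 30 | 5.1%; 5.0% | 4.9%; 4.5% | 3.8%; 3.6% |
| H1a day 2; day 3 | 80 / 30 | 6.4%; 5.6% | 5.5%; 5.1% | 4.4%; 4.0% |
| H2b LICI, 10 days | 35 / 21 | 12.0% | 7.6% | 3.7% |
| H2b LICI, 10 days | 40 / 21 | 11.0% | 6.2% | 3.9% |
| H2b LICI, 2 occasions | 35 / 13 | 9.5% | 6.3% | 3.2% |

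**Mechanism check.** Mean estimated standard error over the true standard deviation of the estimate:
- H1a overall, 70 subjects: 0.284 / 0.316 = 0.90, 10% too small. The implied error is the two-sided tail beyond 1.96 × 0.90 = 1.76, or 7.8%.
- H2b, 35 subjects, 10 days: 0.194 / 0.237 = 0.82, 18% too small. The tail beyond 1.60 is 10.9%.
- H2b, 40 subjects: 0.182 / 0.215 = 0.85. Two occasions: 0.265 / 0.310 = 0.85. Both are about 15% too small.

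The shrunken standard error accounts for most of the excess.

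**Other settings.** A separate simulation with latent correlation 0.50 or 0.75, carrying two LICI values over days 1-5 and 6-10, gave 7.1% and 6.7% for H1a overall and 12.8% and 10.3% for H2b. With Kauermann-Carroll and a t reference these became 5.1% and 4.5% (H1a) and 7.4% and 5.4% (H2b). A further simulation gave about 6% (H1a overall) and about 10% (H2b, standard error about 17% too small), with Mancl-DeRouen bringing both to about 4%.

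**The case against.** The strongest objection is that the protocol does not commit to this analysis. The sandwich is only to be considered, no text calls it uncorrected, and the interval's construction is not given. A finite-sample correction is a detail that a statistical analysis plan, not shown here, may well supply. That stands, so the point is conditional on the sandwich being used as named.

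A reader might infer more than the documents support:
- *That the protocol prescribes an uncorrected sandwich.* It is silent, and silence is not a prescription.
- *That all the GEE tests exceed 5%.* The day-2 and day-3 effects are close to nominal, and a score version of the 9-df interaction test is below it. The Hypothesis 1a text does not choose Wald over score.
- *That about 30 parameters on 70 subjects cause the H1a excess.* The rate is 8.2% with 14 parameters or 30, and the text does not fix time as categorical.
- *That H2b runs at 12 to 13% whatever is done.* Those figures need LICI entered on all 10 days. With only the two measured occasions the rate is 9.5%.

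It is also fair that up to 80 subjects may be analysed, which trims the excess, and that making the sandwich optional matters more. Without it, an independence working correlation gave about 33 to 36% error for H1a overall and for H2b over 10 days. That is a separate matter, and requiring the sandwich alone would still leave H2b at about 9 to 13%. Score tests reduce the H2b error but do not repair a Wald interval.

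**Conclusion.** The point holds in a limited, conditional form. If the sandwich is applied without a small-sample correction, Wald 95% intervals and tests are too liberal for two estimates:
- mainly the H2b LICI odds ratio: 35 to 40 subjects, about 9 to 13% error, standard errors about 15 to 18% too small;
- mildly the H1a overall odds ratio: 70 to 80 subjects, about 6 to 8% error.

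The H2b excess persists with all 40 active subjects and with only the two measured LICI occasions. Its exact size depends on how LICI is entered. All rates rest on the assumed independence working correlation, outcome distribution and within-subject correlation. This is a cheap improvement to consider. It does not invalidate the primary analysis.

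**What to change.** Add one sentence to Section 7.2 or the statistical analysis plan: when the robust variance is used, it carries a small-sample correction (for example Mancl-DeRouen or Kauermann-Carroll) for the H1a overall and H2b odds ratios and for the GEEs built on the same framework (H1b and H3b). Test the 9-df treatment-by-time interaction, if time is categorical, with a generalized score or re-randomisation test, because Mancl-DeRouen leaves its Wald version at 8.8%. State how the two LICI values enter the H2b model.

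The cost is slightly wider intervals and a macro or R call outside PROC GENMOD. Adding a t reference to Mancl-DeRouen makes H2b conservative (2.2% with 35 subjects, against 3.7% without it), so that choice should be made deliberately. The sample size does not change.
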